**Methods:**

The (POMPAE) trial is a phase 2, single-center, double-blinded randomized superiority clinical study. It aims to assess the impact of perioperative continuous intravenous magnesium administration on the occurrence of cardiac surgery-related POAF. A total of 530 patients will be included. Eligible patients will be randomized in 1:1 ratio to the intervention or placebo group with stratification based on the presence of valvular surgery. The objective of the infusion is to maintain ionized magnesium levels between 1.5 and 2.0 mmol/L.

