Baseline (if informed consent obtained)	• Gender, height and weight, EuroScore II • Previous medical history including previous CVA (i/h), MI, PCI, cardiac surgery • Comorbidities including hypertension, dyslipidaemia, asthma/COPD, chronic renal failure, diabetes mellitus, thyroid disease and OSAS • History of smoking including pack years • Left ventricular ejection fraction (%) on preoperative echo
Perioperative data	• Date and time of hospital admission, serum Mg, ECG (rhythm, rate, conduction intervals) • Date and time of initiation of anaesthesia, intubation, start and end of surgery • Date and time of initiation of bolus study medication and continuous infusion including Mg level post induction • Duration of aortic clamp, CPB, type and amount of cardioplegia used • Rescue therapies during surgery (use of medication including circulatory support, assist devices, pacemakers, etc.)
Intensive care	• Date and time of admission/discharge to ICU, extubation, use of circulatory support (type, dosage and duration) and discharge including destination • Mg and ECG data including date and time stamp and alterations to the study medication • Use of antiarrhythmic medications including beta blockers, Mg (unlabelled) amiodarone, etc • Procedures including re-surgery, pacing (in- and external)
Ward/CCU	• Date and time of admission/discharge to the ward/CCU, use of circulatory support (type, dosage and duration) • Continue ECG daily • Use of antiarrhythmic medications including beta blockers, Mg (unlabelled) amiodarone, etc • Procedures including re-surgery, pacing (in- and external)
Outcome and assessment data	• Outcome of the admission (discharged alive, lost to follow-up or diseased) • Other complications including pulmonary embolism, stroke, delirium (required usage of newly described anti-psychotics) or infections requiring antibiotics
Adverse events	• Adverse event description, timing, causality and resolution until discharge • The same was employed for serious adverse events and SUSAR
Protocol deviations	• Occurrence, description including date and time • Exclusion based on logistics (medication does not present at time of surgery, Mg level expired or other with description) • Stopping rule encountered, description including date and time

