### Sample size and power

With 500 patients, this study will have 80% power (2-sided *p* value of 0.05) to detect a relative reduction of 40% (absolute reduction 25% vs 15%) in the incidence of POAF. To allow for consent refusal or loss to follow-up, 530 patients will be recruited.

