### Statistical analysis plan

All analysis will be performed based on modified intention-to-treat principles, excluding only patients that withdrew consent or were unable to receive study medication due to logistical reasons. All eligible patients consenting to participate will be screened and randomized to maximize inclusion. However, as study medication could not be prepared by the pharmacy department outside of regular working hours, patients not able to receive medication at the start of anaesthesia, despite consent, will be excluded from analysis.

All data will initially be assessed for normality. Baseline imbalance will be determined using chi-square tests for equal proportion, Student tests for normally distributed data and Wilcoxon rank sum test for non-parametric data with results presented and *n* (%), mean (standard deviation) or median (interquartile range) respectively.

The primary outcome (POAF) and other binomial secondary outcomes will be analysed using generalized modelling (accounting for stratification variables of surgery type) with relative risk (95% CI) determined using a log binomial model. A risk difference (95% CI) determined using a binomial distribution with an identify link and odds ratios (95% CI) using a logistic binomial model will also be employed, where appropriate. Moreover, it is prescribed that sensitivity analysis will be performed adjusting for baseline imbalance (*p* < 0.2) and baseline covariates previously identified as being known to be linked to outcome (age, left ventricular function, type and length of surgery including time on CPB, use of vasopressors and inotropes). Where there is missing data for the primary outcome, multiple imputation will be employed.

To account for the competing risk of death, duration outcomes (time to POAF, lengths of stay, ventilation, inotropic or vasopressor support) will be analysed using competing risk regression with results reported as hazard ratios (95% CI) and presented as cumulative incidence curves. All analysis will be performed using SAS version 9.4 (SAS Institute Inc., Cary, NC, USA) and a two-sided *p* value of 0.05 will be used to indicate statistical significance. For the analysis of the secondary endpoints, adjustment for multiplicity will be performed using the Holm-Bonferroni method to reduce changes of type 1 error.

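### The primary POAF model adjusts for surgery stratum only, so it forgoes a modest gain in precision from age and LVEF, which the plan already treats as predictors

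*Protocol article*

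**What the plan says.** The protocol article's Statistical analysis plan section sets the primary analysis as a log-binomial model for the relative risk: "The primary outcome (POAF) and other binomial secondary outcomes will be analysed using generalized modelling (accounting for stratification variables of surgery type"). The only covariate beside treatment arm is therefore the surgery stratum. This matches the design, in which patients are "randomized in 1:1 ratio to the intervention or placebo group with stratification based on the presence of valvular surgery".

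Age and left ventricular function appear a few lines later, in a sensitivity analysis. That analysis adjusts for variables showing baseline imbalance at p < 0.2 and for "baseline covariates previously identified as being known to be linked to outcome (age, left ventricular function", followed by type and length of surgery, bypass time, and vasopressor and inotrope use. No reason is given for keeping age and ventricular function out of the primary model.

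Both are available before treatment. The baseline row of Table 2 lists "Left ventricular ejection fraction (%) on preoperative echo", and age is checked as an eligibility criterion in Table 1.

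**The concern.** When the outcome depends on variables fixed before randomisation, a pre-specified adjustment for them removes explained variation from the treatment comparison. With standardisation the target stays the same marginal relative risk or risk difference, and the standard error falls in proportion to how well the covariates predict. The plan itself identifies two such predictors and intends to use them, but not where they would help the primary question.

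The planned sensitivity analysis does not provide this gain in clean form. It mixes age and ventricular function with covariates picked by a baseline test. It also includes length of surgery, bypass time and vasopressor or inotrope use, which arise after randomisation and, at least in part, after study drug starts at induction. The plan thus has no cleanly pre-specified adjusted estimate based on pre-randomisation variables alone.

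At stake are a few points of power and a slightly narrower interval, in a trial sized at exactly 80%.

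**Working it through.** **Inputs from the document**
- Size and power: "With 500 patients, this study will have 80% power (2-sided"; significance level: "value of 0.05 will be used to indicate statistical significance".
- Effect: "to detect a relative reduction of 40% (absolute reduction 25% vs 15%) in the incidence of POAF".
- Allocation 1:1, so 250 per arm.
- Recruitment: "To allow for consent refusal or loss to follow-up, 530 patients will be recruited".

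**Assumed, because the document does not give it:** how strongly age and LVEF predict POAF. A range is shown.

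**Step 1. Reproduce the stated size.** Pooled two-proportion formula, no continuity correction, mean rate 0.20:

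n per arm = [1.960·√(2·0.20·0.80) + 0.8416·√(0.25·0.75 + 0.15·0.85)]² / 0.10²
= [1.960·0.5657 + 0.8416·0.5612]² / 0.01
= (1.1087 + 0.4724)² / 0.01 ≈ 250.

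Total 500, power 80.0%. The plan's figure reproduces exactly.

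**Step 2. Analytic effect of adjustment.** If age and LVEF explain an extra fraction R² of outcome variance beyond the stratum, the adjusted variance is (1 − R²) times the stratum-only variance. The effective size per arm is then 250/(1 − R²), and the interval width scales by √(1 − R²).

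Power = Φ{[0.10·√(250/(1 − R²)) − 1.1087] / 0.5612}

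| Extra R² | Effective total N | Power | CI width ratio |
|---|---|---|---|
| 0 | 500 | 80.0% | 1.000 |
| 0.01 | 505 | 80.4% | 0.995 |
| 0.02 | 510 | 80.8% | 0.990 |
| 0.05 | 526 | 82.0% | 0.975 |
| 0.08 | 543 | 83.2% | 0.959 |
| 0.10 | 556 | 84.0% | 0.949 |

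**Step 3. Simulation check.** 4000 trials per row, n = 500, stratified 1:1, marginal risks 25% and 15%. Assumed: 40% of patients in the valve stratum, log odds ratio 0.5 for that stratum, and standardised age and LVEF. The log relative risk comes from standardising a logistic model, with stratum only and with stratum plus age and LVEF.

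| AUC of age + LVEF | Variance ratio | Power, stratum only | Power, adjusted |
|---|---|---|---|
| 0.50 (no value) | 1.004 | 81.0% | 80.8% |
| 0.59 | 0.988 | 80.8% | 81.0% |
| 0.62 | 0.972 | 79.0% | 80.7% |
| 0.67 | 0.939 | 79.7% | 82.6% |
| 0.71 | 0.916 | 80.7% | 84.4% |

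The stratum-only column should be nearly constant but varies from 79.0% to 81.0%. The Monte Carlo standard error is √(0.8·0.2/4000) ≈ 0.6 points. The variance ratios and the analytic table are therefore the better guide to size. For example, a variance ratio of 0.939 (R² = 0.061) gives about 82.4% by the Step 2 formula, a gain of 2.4 points against the simulated 2.9. In separate null simulations the adjusted test rejected in 4.9% to 5.0% of trials.

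**The case against.** The strongest reply is that nothing here is wrong. The primary model follows the randomisation, the sample size rests on an unadjusted comparison, and the trial reaches its stated power without any change. That stands. A reader might infer that the primary analysis is biased or that the trial is underpowered; the document supports neither.

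The gain is also small and its size is assumed. That stands too. Gains near 4 points need an AUC of about 0.71 from age and LVEF alone, and nothing in the document shows such strength. At an AUC near 0.6 the gain is around one point or less.

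A reader might also say that there is no reserve at all. The recruitment target of 530 qualifies this: if nobody were lost, 265 per arm would give 82.3%. But those 30 patients are set aside for refusal and loss, so they cannot be counted on.

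Timing is a fair objection. The Trial status section says that recruitment is paused pending the interim results, so a change now must be shown to be uninfluenced by them, and the interim will have used the stratum-only model. This calls for safeguards but does not remove the benefit.

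Finally, the gain is not entirely free. Log-binomial and identity-link models with continuous covariates can fail to converge, and missing LVEF needs a rule. Both can be settled in the amendment.

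That an adjusted analysis is already planned is a weaker reply, given the post-randomisation and p-value-selected variables in that analysis.

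**Conclusion.** The point holds as one of lost efficiency, not error. The stratum-only analysis is valid and gives 80.0% power at 500 patients. Adding age and preoperative LVEF would raise power to about 80.4% to 84.0% and narrow the interval by about 0.5% to 5%, equivalent to roughly 5 to 56 extra patients. This rests on an assumed extra R² of 0.01 to 0.10. If the two variables have no prognostic value, the gain is nil and the loss negligible.

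The gain applies to the marginal relative risk and risk difference. It does not carry over to an adjusted odds ratio, which is a different, conditional quantity whose interval need not narrow. Because the plan itself calls these variables predictive and intends to use them, the change is worth making, but the trial's validity does not depend on it.

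**What to change.** Issue a dated amendment, written by staff blinded to interim results and before final unblinding, that:

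- makes the final primary estimate the relative risk, with the risk difference, adjusted for surgery stratum, age (continuous) and preoperative LVEF;
- obtains it by standardisation: fit one logistic model, predict every patient's risk under each arm, average, then take the ratio and the difference, which avoids log-binomial convergence failure;
- fills missing baseline LVEF by a stated simple imputation, so that no patient is dropped;
- keeps the stratum-only log-binomial estimate as supportive and consistent with the interim model;
- keeps length of surgery, bypass time, vasopressor or inotrope use, and any covariate chosen by p < 0.2 out of the primary model.

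The sponsor should also confirm that age is recorded. It is not itemised in Table 2 and the database holds no dates of birth, although the planned sensitivity analysis needs it in any case.

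The cost is a paragraph of analysis wording, a short program, a documented amendment and a primary estimate that is slightly harder to explain. No additional patients are needed.

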## Background

Postoperative atrial fibrillation (POAF) is common after cardiothoracic surgery, affecting approximately 20–40% of patients [1, 2]. As such, POAF is associated with postoperative sequelae, including an elevated susceptibility to stroke, prolonged hospitalization and higher mortality rates [2–4].

Numerous pharmacological agents have undergone scrutiny as potential prophylactic interventions for POAF, including anti-arrhythmic drugs like amiodarone, beta-adrenergic receptor blockers and magnesium [5–8]. Regrettably, no prophylactic regimen has been conclusively established thus far.

Magnesium, a well-recognized and safe mineral, has garnered attention due to its potential to mitigate the risk of POAF. Hypomagnesaemia has been consistently linked to a greater risk of arrhythmias across diverse patient populations, including those undergoing cardiac surgery [9, 10]. The precise mechanistic underpinnings of the magnesium-arrhythmia interplay remain incompletely elucidated but may involve modulation of calcium channel function and the sodium–potassium membrane pump [11]. Magnesium supplementation, therefore, holds promise as an effective modality for attenuating early afterdepolarization-mediated triggered activity in the atria, thereby reducing the risk of POAF [2].

Several studies have demonstrated a reduction in arrhythmic incidents with magnesium supplementation, though these investigations are typically non-randomized and exhibit heterogeneity in dosing regimens and administration routes [11]. A recent pilot study adopting a serum magnesium target range of 1.5–2.0 mmol/L demonstrated a substantial diminution in POAF incidence, underscoring magnesium’s potential as a prophylactic intervention in cardiac surgery patient cohorts [8].

This manuscript describes the study protocol for the ‘PeriOperative Magnesium Infusion to Prevent Atrial Fibrillation Evaluated (POMPAE)’ trial, a double-blinded, placebo-controlled, randomized study. The primary research objective is to assess the efficacy of magnesium supplementation during the perioperative phase of cardiac surgery, with the aim of achieving targeted serum (ionized) magnesium levels within the range of 1.5 to 2.0 mmol/L.

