**Fig. 2 Fig2:**
[figure not shown]
Study protocol for administration of study medication (bolus and/or continuous infusion). Legend: This flowchart shows the study protocol for the measurement of (ionized) magnesium levels and administration of study medication. Patient randomization is not shown within the figure. This event occurs as part of the first step after which a magnesium serum level (part of regular clinical routine) is determined. This level (maximum of 72 h before start of surgery/induction of anaesthesia) determines the procedures undertaken post induction of anaesthesia. (See ‘Trial intervention’ for more details). If magnesium levels fall below 1.0 mmol/L, an unlabelled bolus of 10 mmol magnesium sulphate is administered to the patient as part of regular clinical practice within the hospital for patients undergoing cardiac surgery

Based on the magnesium level taken prior to surgery (maximum of 72 h before surgery), the anaesthesiologist will initiate the study medication after induction of anaesthesia. If magnesium level is below 1.0 mmol/L, a bolus of magnesium is provided, and the continuous infusion is initiated as soon as the central line is in situ.

In general, the aim of the study is to achieve stable magnesium level between 1.5 and 2.0 mmol/L within the intervention group. If the magnesium levels fall below 1.5 mmol/L, a bolus of 10 mmol magnesium sulphate will be given. The continuous infusion is initiated or continued based on the protocol with a trail drug administration rate of 3.0 mmol per hour. In case magnesium levels are above 2.0 mmol/L, the trial medication is (temporarily) ceased. Magnesium levels are measured each 6 h and the study medication is adjusted based on its level as described study protocol.

After discharge from ICU, the study medication in ceased. In the case of readmission to ICU, no trial medication will be initiated as the trial only focuses on the direct perioperative course of a patient during the index operation and the post-surgery ICU admission.

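### The fixed covariate list for the adjusted POAF sensitivity analysis leaves out preoperative ionised magnesium, which is already measured and recorded

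*Protocol article*

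**What the plan says.** All references are to the protocol article.

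- **Statistical analysis plan.** POAF is analysed with a generalised model that accounts for the surgery-type stratum. A sensitivity analysis then adjusts for two sets of variables: those showing baseline imbalance at p < 0.2, and "baseline covariates previously identified as being known to be linked to outcome (age, left ventricular function, type and length of surgery". The second set continues with time on bypass and use of vasopressors and inotropes, and ends there. Magnesium is not named.
- **Background.** "Hypomagnesaemia has been consistently linked to a greater risk of arrhythmias across diverse patient populations, including those undergoing cardiac surgery".
- **Randomization and treatment masking; Trial intervention.** A magnesium level comes from routine admission bloods. The anaesthesiologist starts study medication "Based on the magnesium level taken prior to surgery (maximum of 72 h before surgery"). Trial design states that every magnesium level mentioned is an ionised level.
- **Table 2.** Serum magnesium at admission is recorded, but under perioperative data and not under baseline.
- **Trial design; Fig. 2 legend; Trial intervention.** A level below 1.0 mmol/L leads to a magnesium bolus. The Fig. 2 legend calls it unlabelled and part of regular practice, so it can reach placebo patients too.
- **Sample size and power.** "With 500 patients, this study will have 80% power" at a "2-sided *p* value of 0.05", for a "relative reduction of 40% (absolute reduction 25% vs 15%) in the incidence of POAF".

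**The concern.** The plan selects its fixed covariates by one criterion: an established link to the outcome. By the protocol's own account of magnesium and arrhythmia, the starting level is an obvious candidate. It is also the quantity that the trial manipulates, and it is one of the triggers for magnesium given in either arm. A reader of the results will ask whether the effect survives adjustment for starting magnesium.

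As written, the answer depends on an imbalance test carried out after the data are in. It is not even certain that magnesium would be tested, since Table 2 does not file it as a baseline variable. Two modest things are at stake: some precision in the adjusted estimate, and a prespecified answer to a foreseeable question. Because the article prints a named list, this is a point about what the plan fixes and not about detail left to a fuller document.

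**Working it through.** **1. Reproduce the plan's own figure.** The inputs are 25% against 15%, two-sided 0.05, 80% power and 1:1 allocation. With pooled variance and no continuity correction:

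n per arm = [1.960·√(2·0.20·0.80) + 0.842·√(0.25·0.75 + 0.15·0.85)]² / 0.10² = (1.109 + 0.472)² / 0.01 ≈ 250.

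That gives 500 in total, with power 80.0% at 250 per arm. The stated sample size reproduces and is not in question.

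**2. How often the imbalance rule admits magnesium.** Under randomisation a valid test gives p < 0.2 in 20% of trials by construction. Simulation (4,000 replicates per setting, 250 per arm) gave 19% to 21%.

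**3. What imbalance the rule can miss.** The SD of the between-arm difference in mean magnesium, in SD units, is √(2/250) = 0.089. The p = 0.2 threshold is 1.2816 × 0.089 = 0.115 SD.

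**4. Effect of such an imbalance.** The documents give no strength of association. The odds ratio (OR) per SD higher magnesium is therefore assumed to be 0.9, 0.75 or 0.6, with overall POAF of 20% (the mean of 25% and 15%). To first order:

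- relative risk shift ≈ exp(0.115 × |ln OR| × (1 − 0.20)) − 1
- share of outcome variance explained ≈ 0.20 × 0.80 × (ln OR)²

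| Assumed OR per SD | \|ln OR\| | Relative risk shift | Variance reduction |
|---|---|---|---|
| 0.9 | 0.105 | about 1% | 0.2% |
| 0.75 | 0.288 | about 3% | 1.3% |
| 0.6 | 0.511 | about 5% | 4.2% |

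On the planned relative risk of 15/25 = 0.60, a 5% shift runs from about 0.60/1.05 = 0.57 to 0.60 × 1.05 = 0.63.

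**5. Simulation check.** A logistic model was used with marginal rates of 25% and 15% and a standard normal covariate, so only the size of the OR matters and not its direction. The table compares the treatment test without and with the covariate.

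| Assumed OR per SD | Power without | Power with |
|---|---|---|
| 1.0 | 79.2% | 78.8% |
| 1.2 | 80.2% | 80.3% |
| 1.5 | 80.5% | 81.3% |
| 2.0 | 81.0% | 83.1% |

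Type I error was 4.6% to 5.4% throughout. The change is about −0.4 to +2 points. It describes what the covariate does inside an adjusted model and is not a revision of the trial's design power.

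**The case against.** The strongest reply is that this touches a sensitivity analysis only. The primary model is stratum-adjusted, randomisation already makes it unbiased with respect to starting magnesium, and choosing one more prognostic covariate is partly taste. That stands, and it sets the weight of the point.

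A second reply is that the p < 0.2 rule already covers the worrying case, because whatever escapes it moves the relative risk by 5% at most in the assumed range. This stands in part. The rule does limit the damage, but it depends on the data and may not be applied to magnesium at all, given where Table 2 files it.

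Four stronger readings are tempting, and the documents do not support them:

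- **That the trial's power would rise, or that patients would be saved.** The stated 80% belongs to the primary test, which the fix does not alter.
- **That the primary result is biased.** A chance imbalance is not bias, and the standard error of the primary estimate already allows for it.
- **That the protocol says the preoperative level predicts POAF.** The Background speaks of hypomagnesaemia and arrhythmias in general. Applying it to the preoperative level and to POAF is a short inference.
- **That open-label magnesium in controls confounds the comparison.** Magnesium given under usual care after randomisation is part of the comparator. The preoperative level is also only one trigger, since Trial intervention refers to a level taken 30 min after induction and to any later low value. How many patients start below 1.0 mmol/L is not stated.

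**Conclusion.** The point holds as a minor improvement. The list is fixed in the text, the protocol's own rationale gives a reason to include starting magnesium, and the value is already collected. An imbalance test that would admit it in about 1 trial in 5 is no substitute for naming it in advance.

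The size is a variance reduction of roughly 0% to 4% in the adjusted estimate, and protection against a relative risk shift of about 1% to 5%. These figures rest on assumed odds ratios of 0.9 to 0.6 per SD, overall POAF of 20%, 250 analysed per arm, and magnesium being unrelated to the covariates already listed. If it is related to them, the gain is smaller. If it has no association with POAF, there is no gain.

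**What to change.** In the Statistical analysis plan, add preoperative ionised magnesium to the fixed covariates of the adjusted POAF sensitivity analysis, whatever any imbalance test shows. Define it as continuous: the last value within 72 h before surgery and before any magnesium bolus or study drug. The reference to a bolus is needed because one may precede the infusion, and a further level is drawn 30 min after induction. A rule worded only as the last value before study drug could pick up a level already changed by magnesium.

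No new data are needed, and the primary analysis and sample size stay as they are. The cost is one model term. The one downside to state is that a further continuous covariate can make a log-binomial or identity-link model harder to converge. The change should be made before unblinding.
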